## Abstract

**Background:**

Gaze anxiety (scopophobia) is a frequently observed and reported symptom that is closely associated with social anxiety disorder (SAD). Considering the efficacy of cognitive behavioral therapy (CBT) for social anxiety, it may also be beneficial for individuals with gaze anxiety. Self‐help CBT can offer a means of early intervention; however, its effectiveness remains unclear.

**Methods:**

This protocol describes the design of a clinical trial aimed at evaluating the efficacy of two self‐help CBT interventions for gaze anxiety. This multicenter randomized controlled trial is planned across 12 institutions in Japan. The participants will be young adults aged 18–30 years who report anxiety and avoidance related to gazes. The enrolled participants will be randomly assigned to either a self‐help book CBT group, a web‐based CBT group, or a control group. The severity of gaze anxiety, as the primary outcome, will be assessed using online questionnaires at baseline, 3 months post‐intervention, and the 6‐month follow‐up, with effectiveness evaluated through statistical analysis using mixed‐effects models.

**Results:**

The clinical trial will be performed from April 2025 to March 2026, and the results of this study are expected to be available by mid‐2026. The results of this trial will provide insights into the effectiveness of self‐help CBT for gaze anxiety (scopophobia).

**Conclusions:**

This trial will examine whether self‐help CBT improves access and whether it is effective for adolescents and young adults with social anxiety, especially gaze anxiety.

## INTRODUCTION

Social anxiety disorder (SAD) is a mental disorder characterized by excessive fear of scrutiny and potential embarrassment in social situations, along with anxiety about negative evaluation by others.^1^ SAD commonly onsets during adolescence and has a lifetime prevalence of approximately 4.0%.^2^ Adults and children with SAD tend to avoid eye contact,^3^, ^4^ and the tendency seems to appear in adolescence due to excessive gaze anxiety.^5^ Being looked at often signals the start of interaction in social situations. If gaze anxiety is severe and leads to the avoidance of others, habituation to gaze anxiety may not occur. This can maintain or even worsen gaze and social anxiety. Therefore, early intervention for people with gaze anxiety before it interferes with their daily lives is important.

Individual cognitive behavioral therapy (CBT) for SAD is significantly effective and has been recommended as a treatment option in treatment guidelines.^6^, ^7^, ^8^, ^9^ However, it is unclear how to effectively deliver this promising treatment for preventive interventions. The reason for this is that individual CBT generally has high time and monetary costs. Self‐help CBT is potentially feasible for reducing gaze anxiety, similar to its effectiveness in treating SAD. Self‐help CBT, which people can perform at home, eliminates the need to miss school or university and has lower implementation costs because there is no therapist facilitating individual sessions. For social anxiety in adolescents and young adults, self‐help CBT on websites has been shown to have an effect; however, it is unclear whether it helps with gaze anxiety.^10^ Self‐help CBT via books without therapist guidance has been shown to improve SAD in two previous randomized controlled trials (RCTs).^11^, ^12^ However, there is limited evidence from RCTs in Asia. Furthermore, the efficacy of self‐help CBT for treating gaze anxiety remains unclear.

A clinical trial was designed to examine the efficacy of a self‐help CBT using a book, developed with the aim of alleviating gaze anxiety, and an internet‐based CBT (ICBT) program for social anxiety. This manuscript details the protocol for this clinical trial.

## METHODS AND ANALYSIS

### Trial design

This study protocol is a multicenter RCT being conducted at 12 research institutions in Japan. Eligible participants will be randomly assigned in a 1:1:1 ratio to one of three groups: self‐help CBT book group, ICBT group, or control group (no‐treatment control).

### Participants

Participants will be recruited from the following universities: Kagoshima University, University of Fukui, Shigakukan University, Naruto University of Education, Jin‐ai University, Hiroshima Cosmopolitan University, Teikyo University, Shujitsu University, Tottori University, Fukushima Gakuin University, Tokyo Rissho Junior College, and Senshu University. Additionally, participant enrollment will be solicited through the research project website. The predetermined inclusion and exclusion criteria outline the specific requirements that potential participants must meet for enrollment in the trial.

Inclusion criteria:
1.A total score of 10 or higher on a measure of gaze anxiety symptoms using the Gaze Anxiety Rating Scale (GARS).^3^
2.Enrollment as a university and graduate student aged between 18 and 30 years.3.Capacity to send and receive electronic mail.4.No planned transfer or withdrawal from their academic institution during the study period.

Exclusion criteria:
1.Presence of mental disorders, including but not limited to major depressive disorder and SAD.2.A history of suicidal ideation or attempts.3.Presence of a progressive medical illness (e.g., cancer).4.Pregnancy or the immediate postpartum period.5.Any condition or behavior deemed by the researchers to render the individual unsuitable for participation in this study (e.g., antisocial behavior).

For participants identified as being at risk for mental health conditions, the researchers from each university will inform the principal investigator ([name]), who has been the study secretariat, to assess their eligibility by using the Mini‐International Neuropsychiatric Interview (MINI).^13^, ^14^

### Intervention

#### Self‐help by using a book group

Participants allocated to the self‐guided book intervention will be instructed to read one chapter (approximately 30–50 pages) per week from the self‐help book on gaze anxiety in young adults, “Escaping the Fear and Anxiety of Others' Gaze.”^15^ This self‐help book was authored by the first author ([name]) and published in October 2024. Table 1 presents the contents of the chapters of the self‐help book. This book has 193 pages long with wide line spacing, and we estimate it takes approximately 150 min to read. Each Monday at noon, participants in this group will automatically receive an announcement detailing the chapters to read for the week and words of encouragement.

**Table 1 pcn570236-tbl-0001:** Time to read on the book and its contents.

Week	Title each chapter	Introduced techniques	Page
１	Why do I feel anxious when people look at me?	Psychoeducation	31
２	Understanding the roots of your gaze anxiety	Cognitive behavioral model	21
３	Steps to overcoming your gaze anxiety	Examining safety behaviors Video feedback Attention shift training Behavioral experiments Social/opinion surveys Ceasing rumination and pre‐ and post‐event processing Processing social trauma in image description	81
４	Let's conquer social situations one by one: Case studies	Anxiety about being seen trembling Fear of making public mistakes and being observed Fear of blushing when looked at Fear of saying the wrong thing and being judged	56
５	As your “gaze anxiety” improves	Relapse prevention	2

#### Self‐help in ICBT group

Participants allocated to this intervention group will be instructed to engage using their own devices in an ICBT program designed to ameliorate social anxiety in adolescents and young adults. The completion of one module per week will be recommended, and automated email reminders encouraging program engagement will be sent to participants every Monday morning. The ICBT program was developed by the first author ([name]) on the e‐learning platform learningBOX (learningBOX Inc., Tatsuno, Japan). The ICBT program is based on the model proposed by Clark and Wells.^16^ The program comprises 10 training sessions focusing on CBT components that are efficacious for SAD. Each module is expected to take about 15 min to complete, and the entire content can be finished in about 150 min. Table 2 outlines the treatment modules of the ICBT program.

**Table 2 pcn570236-tbl-0002:** Treatment module of the internet‐based cognitive behavioral therapy (ICBT) program.

Week	Module
1	Psychoeducation and case‐formulation using the cognitive behavioral model
2	Examining safety behaviors and self‐focused attention
3	Video feedback to correct negative self‐image
4	Attention shift training
5	Behavioral experiments
6	Opinion survey
7	Ceasing rumination and pre‐ and post‐event processing
8	Processing social trauma in image description
9	Schema work
10	Relapse prevention

#### Control group

The control group will receive no active intervention during the study period; however, the self‐help book will be sent via mail to the participants upon study completion. While participants in the control group will be permitted to seek usual care, such as counseling, they will be asked to refrain from accessing information specifically related to CBT.

### Outcome

All outcome measures will be structured as web‐based questionnaires and sent to the participants' email addresses at baseline, post‐intervention (5 weeks follow‐up), 3 months follow‐up, and 6 months follow‐up. To promote participant retention and follow‐up completion, monthly email reminders will be sent from the start of the intervention until the end of the follow‐up period. Any deviations from the trial intervention will be recorded during follow‐up assessments.

The primary outcome will be the GARS used to measure the severity of clinical symptoms and rate anxiety/fear and avoidance of gaze. The GARS comprises 17 items regarding social situations involving focused gaze.^3^ For each item, participants will rate the degree of anxiety/fear and the frequency of avoidance on a scale from 0 (“no anxiety” or “no avoidance”) to 3 (“a lot of anxiety” or “avoid a lot”). The total GARS score ranges from 0 to 102, with higher scores indicating a greater severity of gaze anxiety. The validity and reliability of the GARS have been demonstrated in the original English and German versions.^3^, ^17^, ^18^ The Japanese version of the Gaze Anxiety Rating Scale (GARS‐j) was developed through translation into Japanese by the first author ([name]) and back‐translation by the second author ([name]), with the resulting text being reviewed by the original scale developers (please refer to the GARS‐j in the Supporting Information).^19^ Furthermore, the validity of the GARS‐j will be examined using baseline responses from this trial. Table 3 shows secondary outcomes.

**Table 3 pcn570236-tbl-0003:** Secondary outcomes.

Outcome	Description
LSAS‐j	The LSAS‐j includes 24 social situations related to “fear or anxiety” and “avoidance,” which participants rank on a 4‐point scale (0 = never, 4 = severe), has a total score range of 0–144.^20^ The Japanese version of the LSAS has demonstrated reliability and validity and is widely used in Japanese clinical and research settings.^21^ Therapeutic response will be defined as a ≥28% decrease in the LSAS total score.^22^ Remission will be defined as an LSAS total score of <35,^23^ consistent with a previous RCT.^10^ Conversely, worsening will be defined as a ≥28% increase in LSAS total score to assess the risk of exacerbating social anxiety.
SPIN	The SPIN is a self‐rating scale that measures 3 characteristic aspects of SAD: fear, avoidance, and physiological arousal.^24^ In the Japanese version of the SPIN, 17 questions are answered on a 5‐point scale, with 0 = not at all applicable and 4 = extremely applicable.^25^
PHQ‐9	Depressive symptoms will be assessed using the Japanese version of the PHQ‐9.^26^ The initial nine items of the PHQ‐9 inquire about the frequency with which symptoms of major depressive disorder have occurred over the past 2 weeks. For each item, participants select a response from 0 (not at all) to 3 (nearly every day), yielding a total score ranging from 0 to 27, with higher scores indicating a greater severity of depressive symptoms.^27^
GAD‐7	Generalized anxiety will be assessed using the Japanese version of the GAD‐7.^26^ The initial seven items of the GAD‐7 inquire about the frequency with which symptoms of generalized anxiety disorder have occurred over the past 2 weeks. For each item, participants select a response from 0 (not at all) to 3 (nearly every day), yielding a total score ranging from 0 to 21, with higher scores indicating a greater severity of generalized anxiety symptoms.^28^

*Note*: We will also calculate recovery rates based on the Improved Access to Psychological Therapies program criteria and improvement (recovery) rates defined as achieving total scores of SPIN < 19 and PHQ‐9 < 10 simultaneously.^29^ This definition has been used as a benchmark for improvement from SAD.

Abbreviations: GAD‐7, Generalized Anxiety Disorder‐7; LSAS‐j, Japanese version of the Liebowitz Social Anxiety Scale; PHQ‐9, Patient Health Questionnaire‐9; SAD, social anxiety disorder; SPIN, Social Phobia Inventory.

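### Remission and recovery are end-state cut-offs with no baseline condition, so participants who enter below them and do not change count as successes and dilute the group contrasts

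*Protocol article*

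**What the plan says.** All the definitions are in the Outcome section, Table 3 and its note.

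- Remission: "Remission will be defined as an LSAS total score of <35".
- Response: "Therapeutic response will be defined as a ≥28% decrease in the LSAS total score".
- Worsening: "worsening will be defined as a ≥28% increase in LSAS total score", meant to capture the risk of making social anxiety worse.
- Recovery: "achieving total scores of SPIN < 19 and PHQ‐9 < 10 simultaneously". The note adds: "This definition has been used as a benchmark for improvement from SAD".
- LSAS-j scoring: 24 situations rated for fear and for avoidance on a scale described as having four points, with anchors and range given as "0 = never, 4 = severe), has a total score range of 0–144".

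Under Participants, the only symptom threshold for entry is GARS of at least 10. The first exclusion criterion is "Presence of mental disorders, including but not limited to major depressive disorder and SAD". No minimum LSAS or SPIN is set. Under Randomization, one balancing factor is baseline LSAS-j below 50 v 50 or more, with no lower bound. The Statistical analysis plan section adopts intention to treat and compares response, remission and worsening between groups with Fisher's exact test, odds ratios and risk ratios. For worsening it adds relative and absolute risk reduction and the number needed to treat. The Discussion calls the sample non-clinical and lists the categorical outcomes among the trial's strengths.

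**The concern.** Remission and recovery are words for change: a person was above a threshold and is now below it. The rules as written test only where a person ends up. That matters little in a sample selected to be above the cut-off. This sample is selected on gaze anxiety, with formally diagnosed SAD and depression removed, so some participants can be expected to meet the end-state before treatment starts.

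Every such person who stays put adds one success to whichever arm they are in. Both arms' rates rise by a similar amount. The risk ratio moves toward 1, and the risk difference shrinks because fewer people can show an effect. Readers would see high remission rates that are partly not remission, and a treatment contrast smaller than the one among people who could remit.

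The 28% rules have a related weakness. They scale with a person's own baseline, so the rise or fall needed is very small when the baseline is low.

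**Working it through.** **1. What follows from the wording alone.** A participant with baseline LSAS 0 to 34 meets the remission definition on entry and is counted as remitted at follow-up if the score stays there. The same holds for anyone entering with SPIN below 19 and PHQ-9 below 10. No entry criterion excludes these people, and the LSAS stratum below 50 has no floor. The article states no figure for any of these binary outcomes, so there is none to reproduce.

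**2. Dilution of the remission contrast.** Inputs, all assumed because the article gives no baseline LSAS distribution:
- q = share with baseline LSAS below 35
- 90% of them are still below at follow-up, equally in each arm
- true remission among the rest is 30% (intervention) v 15% (control), so the true RR is 2.0 and the true difference is 15 points

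Counted rate = q × 0.90 + (1 − q) × true rate.

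| q | Intervention | Control | RR | Difference (points) |
|---|---|---|---|---|
| 0 | 30.0% | 15.0% | 2.00 | 15.0 |
| 15% | 0.135 + 0.255 = 39.0% | 0.135 + 0.1275 = 26.25% | 1.49 | 12.75 |
| 27% | 0.243 + 0.219 = 46.2% | 0.243 + 0.1095 = 35.25% | 1.31 | 10.95 |
| 40% | 0.36 + 0.18 = 54.0% | 0.36 + 0.09 = 45.0% | 1.20 | 9.0 |

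As a guide to q, a normal LSAS distribution truncated to 0–144, with an assumed mean of 40 to 60 and SD of 20 to 25, puts 10% to 39% below 35.

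**3. Does restricting the denominator cost power?** A second illustration assumes 83 per arm (249 / 3), 10% v 30% true remission in those at 35 or above, and everyone already below staying there.

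| q | Power, all counted | Power, baseline ≥35 only |
|---|---|---|
| 20% | 0.58 (28% v 44%) | 0.83 |
| 40% | 0.34 (46% v 58%) | 0.71 |

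With 69 per arm (207 / 3) the pairs are 0.50 v 0.75 and 0.29 v 0.63. Under these assumptions the smaller denominator is more than repaid by the undiluted contrast.

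**4. Worsening.** The smallest qualifying whole-point rise is 0.28 × baseline, rounded up:
- baseline 10: 2.8, so 3 points
- baseline 20: 5.6, so 6 points
- baseline 50: 14 points
- baseline 60: 16.8, so 17 points
- baseline 0: a percentage change is undefined

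With no true change and an assumed measurement SD of 5, the chance of being labelled worsened is 1 − Φ(0.28 × baseline / (√2 × 5)): 35% at 10, 21% at 20, 2.4% at 50 and 0.9% at 60. Averaged over the distributions assumed in step 2, this is about 3% to 10% overall, because few participants sit at very low scores (0.5% to about 6.5% at LSAS 10 or less). The response rule needs equally small falls at low baselines.

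**5. LSAS anchor.** 24 situations × 2 ratings × 3 = 144, the stated maximum. An upper anchor of 4 would give 24 × 2 × 4 = 192 and five response points, not four.

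**The case against.** **Denominators may be fixed elsewhere.** The article does not say in so many words that everyone is counted, and a full analysis plan could restrict the denominator. The recovery note also points to external service criteria that cannot be checked here. This lowers confidence somewhat, more for recovery than for remission. It does not remove the point: the rules are stated, they carry no baseline condition, and the analysis is by intention to treat.

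**The cut-offs are not all documented as SAD thresholds.** This stands. The article says so only for the SPIN/PHQ-9 definition. The LSAS cut-off is supported by sources not shown, and the worsening rule simply mirrors the response rule. The point rests on the missing baseline condition, not on where the cut-offs came from.

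**A reader might infer that the rates would mostly describe people who were never ill.** The documents do not support that. In the model of step 2, at q = 10% those already below supply 25% of counted remitters in the intervention arm (0.09 / 0.36) and 40% in control (0.09 / 0.225). At 27% the figures are 53% and 69%. The true share is unknown, and a score below a cut-off is not the same as never having been ill.

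**A reader might also infer that the worsening measure is swamped by noise.** That comes from looking only at the low-baseline rows. Weighted over plausible baselines, chance worsening is about 3% to 10%.

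**Other safeguards exist.** Mean LSAS change is already planned in the mixed models. Adverse events are collected, and PHQ-9 scores of 10 or more lead to a MINI assessment. Balancing on LSAS limits chance imbalance in the low-baseline share. All true, but none of this repairs the remission and recovery definitions.

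**Conclusion.** The point holds for remission and recovery. As defined, they count unchanged low scorers as successes, in a sample whose entry rules admit such people. The consequence is inflated rates and contrasts attenuated toward no effect. Under the stated assumptions a true RR of 2.0 would be reported as 1.49 to 1.20, and a 15-point difference as about 13 to 9 points. The direction follows from the definitions provided that those already below behave alike in each arm; the size rests on an assumed baseline share.

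The 28% worsening and response rules have the same kind of weakness to a smaller degree, confined to low baselines. The LSAS anchor is a clerical slip that the same sentence resolves through its four-point scale and its 0–144 range; it has no bearing on the main point.

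These are secondary outcomes. Randomisation spreads the already-below participants across arms on average, so no arm is favoured, and the primary GARS analysis is untouched.

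**What to change.** 1. Define LSAS remission among participants with baseline LSAS of 35 or more.
2. Define SPIN/PHQ-9 recovery among participants who do not already meet it at baseline.
3. As a supplementary check, report worsening and response separately for baseline LSAS below 50 and 50 or more, and say how a baseline of 0 is handled. This stratum is already used in randomisation. It is preferable to a fixed minimum number of points, which would be arbitrary and could hide real harm: with a 10-point floor, for example, a rise from 20 to 29 (45%) would no longer count as worsening.
4. Correct the upper LSAS anchor from 4 to 3, to agree with the four-point scale and the 0–144 range.

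Items 1 and 2 condition only on baseline values, so the comparison stays randomised. The cost is wording in the protocol or analysis plan and smaller denominators for remission and recovery. The numbers excluded in each arm should be reported alongside.

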### Sample size

The sample size for this study was set at 249 (Figure 1), considering the following G*Power estimated values and a 20% attrition rate (version 3.1.9.7; The G*Power Team).^30^, ^31^ We set the parameters for the *F* tests—anova: fixed effects, omnibus, one‐way, with an effect size *F* = 0.25 (medium), an *α* error probability of 0.05, and a power (1 − *β* error probability) of 0.9 for three groups. These inputs yielded a noncentrality parameter of 12.94, a critical *F* of 3.04, an original total sample size of 207, and an actual power of 0.902.

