### Statistical analysis plan

Statistical analyses will be performed by the second author ([name]) using IBM spss Statistics (IBM Corp., Armonk, NY, USA) and will adhere to the intention‐to‐treat principle. The analyst was not involved in creating the two intervention programs. The analyst will be concealed to group allocation when accessing the data. This means she will not know which specific intervention a group received or if each participant was in the control condition.

Descriptive statistics will be used to summarize demographic data (including participants' age and sex) and the severity of clinical symptoms on each scale. Group differences will be compared to determine statistical significance. As a primary analysis, mixed‐effects models will examine significant differences in the mean change in total scores on each symptom rating scale between the groups from baseline to Week 5 (1 month), Week 13 (3 months), and Week 26 (6 months) post‐intervention. If an overall significant difference is found, multiple comparisons will be conducted. For multiple comparisons, we will implement Dunnett's test to control for inflated Type I error rates.^33^ Effect sizes will be calculated between and within the groups. The significance level for hypothesis testing will be set at a two‐tailed *α* of 0.05, and 95% two‐sided confidence intervals will be calculated.

For the binary variables of treatment response, remission, and worsening, the odds and risk ratios between the groups will be analyzed using Fisher's exact test. To further evaluate the risk of worsening social anxiety, as measured by the LSAS, we will calculate the risk ratio, relative risk reduction, absolute risk reduction, and number needed to treat.

We plan to conduct a sensitivity analysis excluding participants with insufficient engagement in the self‐help intervention and those who provided implausible response patterns—specifically, patterns like straight‐lining, contradictory responses, or inconsistent responses between the GARS‐j and the LSAS‐j. Participants will be defined as having sufficient engagement if those in the self‐help book group have completed at least two chapters, and those in the ICBT group have reached the “Behavioral Experiments” treatment module. The sensitivity analysis, similar to the primary analysis, will be performed after imputing missing values using R's “mice” package.^34^

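### The sample size of 249 does not keep 207 participants after 20% attrition: 207 appears to have been multiplied by 1.2 instead of divided by 0.8

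*Protocol article*

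**What the plan says.** The Sample size section of the protocol article sets the number to enrol in one sentence: "The sample size for this study was set at 249 (Figure 1), considering the following G*Power estimated values and a 20% attrition rate". The calculation behind it is an ANOVA F test, described as "fixed effects, omnibus, one‐way, with an effect size" of 0.25, with an alpha "error probability of 0.05" and a target power (1 − beta "error probability) of 0.9 for three groups"). The reported output includes a noncentrality parameter of 12.94, a critical F of 3.04, and "an original total sample size of 207, and an actual power of 0.902".

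The only allowance mentioned between 207 and 249 is "a 20% attrition rate". The section gives no inflation formula, and no other section explains the step. The Trial design section specifies 1:1:1 allocation to three groups, so 207 is 69 per arm and 249 is 83 per arm.

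**The concern.** The ANOVA calculation takes the number of participants analysed as its input, so 207 is the number that must still be there at analysis. An attrition rate of 20% means that one in five of those enrolled is lost and 80% remain. The enrolment target therefore has to be the analysed number divided by 0.80. Adding 20% of 207 to 207 takes the percentage of the wrong base and gives too small a total.

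The purpose of the allowance is to protect the power target. If it is computed on the wrong base, an enrolment of 249, 20% attrition and power of 0.90 cannot all hold together under the protocol's own sizing method. A reader would take the trial to have slightly more protection against dropout than it has.

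**Working it through.** **Inputs** (all from the Sample size section, except the allocation ratio, which is in Trial design): k = 3 groups, f = 0.25, alpha = 0.05, target power 0.90, pre-attrition N = 207, attrition 20%, enrolment 249, allocation 1:1:1.

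**Step 1. Reproduce the pre-attrition figure.** For the omnibus F test, lambda = f² × N, with k − 1 and N − k degrees of freedom.

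- lambda = 0.25² × 207 = 0.0625 × 207 = 12.9375 (stated: 12.94)
- critical F with 2 and 204 degrees of freedom = 3.040 (stated: 3.04)
- power from the noncentral F distribution = 0.9022 (stated: 0.902)

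The smallest multiple of 3 with power of at least 0.90 is 207. This part of the calculation is correct.

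**Step 2. Inflate for 20% attrition.** The enrolment needed is N / (1 − d).

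- In total: 207 / 0.80 = 258.75, so 259
- Per arm: 69 / 0.80 = 86.25, so 87, or 3 × 87 = 261 in total

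**Step 3. Find what gives 249.** The alternative is N × (1 + d).

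- In total: 207 × 1.20 = 248.4, so 249
- Per arm: 69 × 1.20 = 82.8, so 83, or 3 × 83 = 249 in total

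The match holds both in total and per arm. The shortfall against Step 2 is 259 − 249 = 10 (10/259 = 3.9%) or 261 − 249 = 12 (12/261 = 4.6%).

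**Step 4. Apply the stated attrition to the stated enrolment.** 249 × 0.80 = 199.2, so about 199 remain, 8 fewer than 207.

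| Analysed N | lambda | Power |
|---|---|---|
| 207 (as stated) | 12.94 | 0.902 |
| 201 (67 per arm) | 12.56 | 0.893 |
| 199 (249 less 20%) | 12.44 | 0.890 |
| 198 (66 per arm) | 12.38 | 0.888 |

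**Step 5. Find the attrition that 249 does cover.** Solving 249 × (1 − d) = 207 gives d = 1 − 207/249 = 42/249 = 0.1687. So 249 keeps 207 participants only if attrition is no more than 16.9%.

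**The case against.** The arithmetic is hard to dispute, but four points can be made about its weight.

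- **The effect is small.** Power of 0.890 is one percentage point below the target. The effect size is a conventional medium value with no trial-specific estimate behind it. At 199 participants, a noncentrality of 12.94 needs f = √(12.94/199) = 0.255, a change well inside the uncertainty of that input. No estimate or test becomes invalid. All of this stands, and it limits the importance of the point.
- **The protocol attaches 0.902 to 207, before attrition.** It never says outright that 207 remain or that power is 0.90 after loss. That is literally true. But an attrition allowance has no purpose other than to preserve the target, and the text offers no other reason for going from 207 to 249.
- **The multiplication by 1.2 is inferred.** This is correct, since the article prints no formula. The finding does not depend on it, because 249 less 20% is about 199 by any route.
- **The planned analysis differs from the sizing model.** The Statistical analysis plan section specifies intention-to-treat mixed-effects models with assessments at Weeks 5, 13 and 26. A participant lost late can still contribute earlier data, so the real loss of information may be smaller. The figure of 0.890 is therefore the power of a one-way ANOVA with dropouts fully excluded, and power for the actual analysis is not established by it. This softens the consequence but does not rescue the step: the section sizes the trial on a one-way ANOVA, takes no credit for repeated measures, and itself chose to inflate for loss.

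**Conclusion.** The concern holds. An enrolment of 249 does not keep 207 participants at 20% attrition. It keeps about 199, for which the protocol's own F test has power of about 0.89 instead of 0.902. The enrolment that matches the stated inputs is 259, or 261 with equal arms.

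The power figure assumes f = 0.25, alpha 0.05, loss spread evenly over the arms, and no contribution from participants who drop out. The arithmetic is certain and every input is printed in the article. The practical effect is modest, about one point of power, and it does not threaten the trial's conclusions. It is still a sample-size statement that is wrong as written and should be corrected.

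**What to change.** Keep 249 and make the sentence true in one of two ways:

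- State that with 20% attrition about 199 participants remain, giving power of 0.89 for f = 0.25 on the one-way ANOVA.
- State that 249 allows for 16.9% attrition while keeping 207 participants and power of 0.902.

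The inflation formula should be printed alongside. The cost is one sentence and a slightly less favourable claim, with no extra participants and no change to the design. If power of 0.90 at 20% attrition is a firm requirement, enrolment has to rise to 259, or to 261 to keep the arms equal, which means 10 to 12 more participants.
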